## **6.3 Safety Data Collection and Management Procedures**

### **6.3.1 Expected Adverse Vaccine Reactions:**

As for any adjuvanted vaccine when administered intra-muscularly, local reactions are expected. Systemic reactions are less often observed, however a standardized data collection of adverse reactions will be organized (see section 7.1).

The clinical experience with Montanide, Alhydrogel and AS02A has shown that the most frequent local reactions are pain, erythema and swelling at the site of injection. Montanide, Alhydrogel are known also to be responsible of induration at the site of injection,

Data on expected systemic reactions is unclear. Therefore, general signs, i.e. fever, headache, fatigue, and drowsiness, will especially be noted.

In case of a severe local skin reaction, either uni-lateral or contra-lateral, a skin biopsy may be part of the procedure as part of the clinical evaluation.

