#### **3.3.2 Diary**

All subjects will receive diary cards which are the source document for the follow-up surveillance during the 14 days after each injection. (see section 7.1)

Diaries will be given to each subject at time of the vaccination visit, i.e. V2, V7 and V13. The diary will contain all solicited local and systemic reactions, as standardised data, as well as open fields for unsolicited reactions/events.

Subjects will be provided with a ruler for daily measurement of the size of local reactions at vaccination sites, and with a thermometer for daily measurement of temperature. The procedures for measurement will be explained each time a diary is provided. At day 3 and 7 after each vaccination, the investigator will check that the data collection is properly done.

The diaries will be collected on the 14-day following each vaccination, i.e. V4, V7, and V11. The data collected in the diary will be reported in the case report form.

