##### **1. Any local**

[figure not shown]

2. **Pain** : Intensity and duration
3. **Redness** : Size (mm) and duration
4. **Swelling**: Size (mm) and duration
5. **Other Local** : Intensity or size and duration

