## 2. *Systemic reactions*

The following systemic reactions will be recorded immediately after the injection (30 minutes) and during the 14 days following the vaccination (D0 and D14 follow-up):

1. **Any systemic**
2. **Fatigue** : Duration and intensity
3. **Fever** : Intensity and duration
4. **Headache** Intensity and duration
5. **Malaise**: Intensity and duration
6. **Myalgia**: Intensity and duration
7. **Joint pain**: Intensity and duration
8. **Gastro-intestinal symptoms**:
  - **Nausea**: Intensity and Duration
  - **Diarrhoea** : Intensity and Duration
  - **Vomiting** : Intensity and Duration
  - **Abdominal pain**: Intensity and Duration
9. **Contro-lateral local reaction** : Intensity and Duration
10. **Other systemic** : Intensity and Duration

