### 7.1.3 Method and Timing of Measurement

#### 1. *Local reactions*

The duration of the **pain** will be measured in minutes, hours or days, and the severity scale as 1) mild: easily tolerated, does not interfere with daily life 2) moderate: discomfort that interferes with or limits usual daily activity 3) severe: disabling, inability to perform usual daily activity, including a functional limitation of the movement.

The duration of redness, swelling, and other local reaction will be measured in hours or in days.

The size of redness, swelling, will be measured in cm with a rule, the maximum length will be reported on the CRF, in mm. **Redness, or swelling**. of less than 20 mm is mild, of 20-50 mm is moderate, and of greater than 50 mm is severe

Solicited local reactions will be recorded at visits V2; V3, V4; V5, V6, V, V8, V9, V10, V11, V13, V14, V15, V16 and V17. The subjects will report daily the local reactions in their diary from day 1 to day 14 after the vaccination.

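### Induration and drowsiness are singled out in section 6.3.1 but are not named solicited items in 7.1.2 or Appendix 3, so their capture, grading and classification are left uncertain

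*Protocol*

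**What the plan says.** Section 6.3.1 describes the expected reactions and refers to section 7.1 for standardised collection. On local reactions it adds that Montanide and Alhydrogel are "known also to be responsible of induration at the site of injection"; AS02A is not mentioned there. On systemic reactions it says "general signs, i.e. fever, headache, fatigue, and drowsiness, will especially be noted".

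Section 7.1.2 lists the local reactions as any local, pain, redness, swelling and Other Local, the last recorded as "Intensity or size and duration". The systemic list covers fatigue, fever, headache, malaise, myalgia, joint pain, four gastro-intestinal symptoms, a contralateral local reaction and "Other systemic". Induration and drowsiness appear in neither list, and Appendix 3 has no row for either.

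On the diary, section 3.3.2 says "The diary will contain all solicited local and systemic reactions, as standardised data", with open fields for anything unsolicited.

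**The concern.** A solicited list should contain the reactions that the protocol itself expects. Section 6.3.1 names two and sends the reader to 7.1, where they are missing. Prompted and unprompted reporting are not equivalent, and a later analysis plan cannot recover what was never asked.

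Four rules depend on how these reactions are captured and classed:

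- **Causality (6.3.4).** Solicited local reactions are related by definition; every other event needs the investigator's judgement.
- **Primary criterion (7.1.1).** Reactogenicity counts in full for 14 days. A non-serious unsolicited event counts only if it led to a physician visit.
- **Severity triggers.** The holding rule in 6.2.2 counts related Grade 3 events. The code-break provision in 3.1.3 looks at severe reactions, defined by reference to 7.1.2, across the three adjuvants.
- **Formulation choice (3.1.1).** A formulation goes forward only if its rate of vaccine-related reactions is low enough.

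**Working it through.** The protocol states no figure on this point, so the check is mainly a comparison of sections.

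**1. Expected reactions against the solicited lists.** Section 6.3.1 gives four general signs. Fever, headache and fatigue are carried into 7.1.2; drowsiness is the only one that is not. Of the local reactions in 6.3.1, pain, erythema and swelling are carried over; induration is not.

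**2. Grading of induration.** Section 6.3.2 ranks local symptoms by the size of the reaction. Section 7.1.3 and Appendix 3 give size bands for redness and swelling only. For the Other Local entry, 7.1.3 adds a rule on duration alone: "The duration of redness, swelling, and other local reaction will be measured in hours or in days". What remains is the general 1 to 3 scale in Appendix 3, which is based on interference with everyday activity. As an illustration, a 60 mm swelling is Grade 3, being above 50 mm. A painless 60 mm induration that does not disturb activity has no size band and would be Grade 1 on the general scale.

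**3. Classification.** Section 6.1.1 says that solicited events are those described in 7.1 and that all others are unsolicited. Other Local is a numbered item in 7.1.2, which suggests solicited. The diary rule in 3.3.2 puts unlisted events in open fields for unsolicited reactions, which suggests the opposite. No sentence settles it.

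**4. Who is affected.** From the group table in 3.1.1, the alum and Montanide groups are Al10, Al50, M10 and M50: 4 × 10 = 40 of 60 subjects. With three doses each, that is 40 × 3 = 120 of 60 × 3 = 180 planned injections. This applies to induration only.

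**5. Possible size, on assumed values.** Let p be the true proportion of a group of 10 with induration and c the proportion of those cases recorded without a named prompt. The protocol gives neither, so both are assumptions.

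Expected recorded cases = 10 × p × c; probability of at least one = 1 − (1 − p × c)^10.

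| p | c | Expected recorded | P(at least one) |
|---|---|---|---|
| 0.30 | 1.00 | 3.0 | 0.97 |
| 0.30 | 0.75 | 2.25 | 0.92 |
| 0.30 | 0.50 | 1.5 | 0.80 |
| 0.30 | 0.25 | 0.75 | 0.54 |
| 0.10 | 1.00 | 1.0 | 0.65 |
| 0.10 | 0.25 | 0.25 | 0.22 |

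With full capture nothing is lost. At p = 0.30, capture of 50% loses 3.0 − 1.5 = 1.5 cases per group.

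**The case against.** The strongest reply is that the protocol has many other ways to record these reactions. Other Local takes intensity or size, and duration; Other systemic takes intensity and duration. The flow chart marks a physical examination at all 19 visits, including 1, 3, 7 and 14 days after each dose, and induration is a physical sign that an examiner can find. Section 6.3.3 requires every adverse event within a month of each dose to be recorded and has the investigator ask at every visit. The instruction in 6.3.1 to note drowsiness is itself a direction to collect it. On a natural reading, Other Local is solicited and therefore automatically related. A subject with induration who also has pain, redness or swelling already counts under any local reaction. Finally, the case report form is not reproduced in the copy at hand, so it may carry lines for both.

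Most of this stands. A reader might infer that expected reactions are certain to be under-counted, or that induration would have no grade at all. The documents support neither: the routes above allow capture, and the general scale allows grading. A reader might also infer that both omissions make some adjuvants look safer than others. That cannot apply to drowsiness, which is linked to no adjuvant. For induration it is only a possibility, in a trial whose analysis is descriptive and which section 3.1.1 says is not built for comparing groups.

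The reply does not remove the gap. The question prescribed in 6.3.3 is general and non-leading, so it prompts for neither reaction by name. The fallback routes supply no size bands for induration and do not settle whether it is solicited. The severity triggers and the per-formulation criterion in 3.1.1 use these data even without a formal group comparison.

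**Conclusion.** The concern holds as a mismatch between 6.3.1 and the lists in 7.1.2 and Appendix 3. It creates a risk, not a demonstrated bias: two reactions that the protocol itself singles out may be captured less often or less consistently, induration may be graded by different rules, and either may be classed differently from one case to the next. For induration the exposure is 40 of 60 subjects; drowsiness has no stated adjuvant-specific effect.

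The size of any under-count cannot be derived from the protocol and may be zero. The figures in the table rest wholly on assumed rates and concern a separate induration rate; the effect on the any-local rate would be smaller wherever other local reactions coincide. The point is worth correcting because the lists feed the primary safety criterion and the correction is cheap.

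**What to change.** Reconcile 6.3.1 with 7.1.2, the diary and Appendix 3 by naming both reactions as solicited items:

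- **Induration:** largest diameter in mm and duration, graded on the size bands already used for redness and swelling. Section 7.1.3 and Appendix 3 place exactly 20 mm in different bands, so the new row should cite one of them.
- **Drowsiness:** intensity and duration, graded like the other systemic symptoms.

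Naming them also settles their class: both count as solicited, and induration is then related by definition under 6.3.4. Stating only that they belong under Other Local and Other systemic, and how those entries count, would resolve the classification but leave both unprompted.

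The cost is two extra lines in the diary and case report form. Recorded reaction rates may rise slightly, which should be borne in mind when they are read against the acceptability threshold in 3.1.1.

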### **6.3.3 Time period, frequency, and method of detecting adverse events and serious adverse events**

All AEs occurring within one month following administration of each dose of vaccine must be recorded on the Adverse Event form in the subject's CRF, irrespective of severity or whether or not they are considered vaccination-related.

The standard time period for collecting and recording SAEs will begin at randomization or the first receipt of vaccine and will end one month following administration of the last dose of study vaccine for each subject. See Section 6.3.4 for instructions for reporting and recording SAEs.

Additionally, in order to fulfil international reporting obligations, SAEs that are related to study participation (e.g. procedures, invasive tests, a change from existing therapy) or are related to a concurrent medication will be collected and recorded from the time the subject consents to participate in the study until she/he is discharged.

The investigator will inquire about the occurrence of AEs/SAEs at every visit/contact during the study and throughout the follow-up phase as appropriate.

All AEs either observed by the investigator or one of his clinical collaborators or reported by the subject spontaneously or in response to a direct question will be evaluated by the investigator. AEs not previously documented in the study will be recorded in the Adverse Event form within the subject's CRF. The nature of each event, date and time (where appropriate) of onset, outcome, intensity and relationship to vaccination should be established. Details of any corrective treatment should be recorded on the appropriate page of the CRF.

As a consistent method of soliciting AEs, the subject should be asked a non-leading question such as:

"Have you felt different in any way since receiving the vaccine or since the previous visit?"

AEs already documented in the CRF, i.e. at a previous assessment, and designated as "not recovered/not resolved" or "recovering/resolving" should be reviewed at subsequent visits, as necessary. If these have resolved, the documentation in the CRF should be completed.

N.B. If an AE changes in frequency or intensity during the specified reporting period, a new record of the event will be entered.

When an AE/SAE occurs, it is the responsibility of the investigator to review all documentation (e.g., hospital progress notes, laboratory, and diagnostics reports) relative to the event. The investigator will then record all relevant information regarding an AE/SAE on the CRF or SAE Report Form respectively. It is not acceptable for the investigator to send photocopies of the subject's medical records to EMVI and GSK Biologicals in lieu of the appropriate completed AE/SAE pages. However, there may be instances when copies of medical records for certain cases are requested by EMVI or GSK Biologicals. In this instance, all subject identifiers will be blinded on the copies of the medical records prior to submission to EMVI and GSK Biologicals.

The investigator will attempt to establish a diagnosis of the event based on signs, symptoms, and/or other clinical information. In such cases, the diagnosis should be documented as the AE/SAE and not the individual signs/symptoms.

[figure not shown]

#### **6.3.4 Assessment of causality**

The investigator is obligated to assess the relationship between investigational product and the occurrence of each AE/SAE. The investigator will use clinical judgement to determine the relationship. Alternative causes, such as natural history of the underlying diseases, concomitant therapy, other risk factors and the temporal relationship of the event to the investigational product will be considered and investigated. The investigator will also consult the Investigator Brochure and/or Product Information, for marketed products, in the determination of his/her assessment.

There may be situations when a SAE has occurred and the investigator has minimal information to include in the initial report to EMVI and GSK Biologicals. However, it is very important that the investigator always makes an assessment of causality for every event prior to transmission of the SAE Report Form to EMVI and GSK Biologicals. The investigator may change his/her opinion of causality in light of follow-up information, amending the SAE Report Form accordingly. The causality assessment is one of the criteria used when determining regulatory reporting requirements.

All solicited local (injection site) reactions will be considered causally related to vaccination. Causality of all other AEs should be assessed by the investigator using the following question:

Is there a reasonable possibility that the AE may have been caused by the investigational product ?

|     |                                                                                                                                                                                                          |
|-----|----------------------------------------------------------------------------------------------------------------------------------------------------------------------------------------------------------|
| NO  | The AE is not causally related to administration of the study vaccine(s). There are other, more likely causes and administration of the study vaccine(s) is not suspected to have contributed to the AE. |
| YES | There is a reasonable possibility that the vaccine(s) contributed to the AE.                                                                                                                             |

Non-serious and serious AEs will be evaluated as two distinct events. If an event meets the criteria to be determined “serious” (see Section 6.1.2 for definition of serious adverse event), it will be examined by the investigator to the extent to be able to determine ALL contributing factors applicable to each serious adverse event.

Other possible contributors include:

- Medical history
- Other medication
- Protocol required procedure
- Other procedure not required by the protocol
- Lack of efficacy of the vaccine(s), if applicable
- Erroneous administration
- Other cause (specify)

#### **6.3.5 Medically attended visits**

For each solicited and unsolicited symptom the subject experiences, the subject will be asked if they received medical attention defined as hospitalization, an emergency room visit or a visit to or from medical personnel (medical doctor) for any reason and this information will be recorded in the CRF.

[figure not shown]

## **6.4 Follow-up of adverse events and serious adverse events and assessment of outcome**

After the initial AE/SAE report, the investigator is required to proactively follow-up on each subject and to provide further information to EMVI and GSK Biologicals on the subject's condition.

All AEs and SAEs documented at a previous visit/contact and designated as not recovered/not resolved or recovering/resolving will be reviewed at subsequent visits/contacts.

Investigators will follow-up subjects:

- with SAEs or subjects withdrawn from the study as a result of an AE, until the event has resolved, subsided, stabilized, disappeared, the event is otherwise explained, or the subject is loss to follow-up;
- or, in the case of other non-serious AEs, until they complete the study or they are loss to follow-up.

Clinically significant laboratory abnormalities will be followed up until they have returned to normal, or a satisfactory explanation, not related to the trial, has been provided. Additional information (including but not limited to laboratory results) relative to the subsequent course of such an abnormality noted for any subject must be made available to the Study Monitor.

EMVI -for all SAEs- and GSK Biologicals –only when AS02 is concerned- may request that the investigator perform or arrange for the conduct of supplemental measurements and/or evaluations to elucidate as fully as possible the nature and/or causality of the AE or SAE. The investigator is obliged to assist. If a subject dies during participation in the study or during a recognized follow-up period, EMVI -for all SAEs- and GSK Biologicals –only when AS02 is concerned- will be provided with a copy of any available post-mortem findings, including histopathology.

New or updated information will be recorded on the originally completed SAE Report Form, with all changes signed and dated by the investigator. The updated SAE report form should be resent to EMVI -for all SAEs- and GSK Biologicals –only when AS02 is concerned- within 24 hours of receipt of the follow-up information as outlined in Section 6.4.2.

Outcome of any non-serious AE occurring within 30 days post-vaccination (i.e. unsolicited AE) or any SAE reported during the entire study will be assessed as:

- Recovered/resolved
- Not recovered/not resolved
- Recovering/resolving
- Recovered with sequelae/resolved with sequelae
- Fatal (SAEs only)

## **6.5 Reporting of Serious Adverse Events**

### **6.5.1 Time frames for reporting of SAEs**

SAEs will be reported promptly once the investigator determines that the event meets the protocol definition of an SAE. The investigator or designate will report to EMVI monitor -for all SAEs- and GSK Biologicals –only when AS02 is concerned- **WITHIN 24 HOURS OF HIS/HER BECOMING AWARE OF THESE EVENTS**. Additional or follow-up information relating to the initial SAE report is also to be

[figure not shown]

reported to the EMVI monitor -for all SAEs- and GSK Biologicals Study Contact for Serious Adverse Event Reporting –only when AS02 is concerned- within 24 hours of receipt of such information.

If information on the adjuvant used is necessary for the treatment of the subject, the code will be broken by the investigator.

The investigator will always inform the safety monitor, who will, in case the code was not broken, break the code for sending the information on AS02 to GSK.

Notification should be made

1. to EMVI for all the SAEs  
by phone; then the investigator should immediately send the **completed SAE report** to EMVI  
or by email or fax by sending the **completed SAE report**, with an acknowledgment of receipt.
2. to GSK for SAEs occurring in the groups receiving the AS02A formulations  
by fax by sending the **completed SAE report**
3. to the IRB

## 6.5.2 Completion and transmission of serious adverse event reports

Once an investigator becomes aware that a SAE has occurred in a study subject, she/he will report the information to the EMVI monitor and in case of AS02 to GSK Biologicals Study Contact for reporting SAEs within 24 hours. The SAE Report Form will always be completed as thoroughly as possible with all available details of the event, signed by the investigator (or designee). If the investigator does not have all information regarding an SAE, he/she will not wait to receive additional information before notifying Study Contact of the event and completing the form. The form will be updated when additional information is received and forwarded to EMVI and eventually to GSK WITHIN 24 HOURS.

The investigator will always provide an assessment of causality at the time of the initial report as described in Section 6.3.4.

Facsimile (Fax) transmission of the SAE Report Form is the preferred method to transmit this information to the Study Contact for Reporting SAEs. In rare circumstances and in the absence of facsimile equipment, notification by telephone is acceptable, with a copy of the SAE Report Form sent by overnight mail. Initial notification via the telephone does not replace the need for the investigator to complete and sign the SAE Report Form within 24 hours.

In the event of a death determined by the investigator to be related to vaccination, sending of the fax must be accompanied by telephone call to EMVI monitor and in case of AS02 involvement to the GSK Biologicals Study Contact for Reporting SAEs.

